### Secondary efficacy endpoints

3.2

(1) change in YGTSS-TTS from baseline and the proportion of participants achieving a ≥ 30% reduction; (2) percentage change in YGTSS-TTS from baseline and the proportion of participants achieving a ≥ 50% reduction; (3) change in YGTSS Total Score from baseline, percentage change, the proportion of participants achieving a ≥ 30% reduction, and the proportion achieving a ≥ 50% reduction; (4) change in YGTSS-IS from baseline; (5)change in the total TCM-SRS score from baseline, the proportion of participants achieving a ≥ 30% reduction, the proportion achieving a ≥ 50% reduction, and change in individual TCM-SRS symptom scores from baseline; and (6) change in the total C&A-GTS-QoL score from baseline. The specific assessment time points are as follows: assessments for the first endpoint will be performed at Weeks 2, 4, and 6, as well as at 4 weeks post-treatment; assessments for the second, third, and fourth endpoints will be performed at Weeks 2, 4, 6, and 8, as well as at 4 weeks post-treatment; assessments for the fifth endpoint will be performed at Weeks 2, 4, 6, and 8; and assessments for the sixth endpoint will be performed at Weeks 4 and 8.

### Safety assessment

3.3

Any adverse events (AEs) during the trial will be reported to investigators and documented in the eCRF, including onset time, severity, causality, seriousness, measures taken, and outcome.

All participants will undergo vital signs, physical examination, laboratory tests (complete blood count, blood biochemistry, urinalysis), and ECG.

During screening, anti-streptolysin O antibody, anti-DNase B antibody, ceruloplasmin, and rheumatoid factor will be tested to exclude rheumatic chorea, Wilson’s disease, and other related disorders, with close monitoring of clinically significant abnormalities.

All AEs will be evaluated and analyzed, and their causality with the study intervention will be assessed.

Serious AEs will be reported to the Ethics Committee and the study team within 24 h.

## Statistical analysis

4

All statistical analyses will be conducted according to a prespecified statistical analysis plan (SAP) by statisticians independent of the research team, who will remain blinded to treatment allocation. A two-sided *P* value <0.05 will be considered statistically significant, and 95% confidence intervals (CIs) will be used to estimate effect sizes. All analyses will be performed using SAS version 9.4 (SAS Institute Inc., Cary, NC, USA).

Continuous variables will be summarized according to their distribution using the number of observations, mean, standard deviation, median, 25th percentile (P25), 75th percentile (P75), and range. Categorical variables will be presented as frequencies and percentages. Demographic characteristics and baseline variables will be summarized descriptively.

For participants who withdraw, drop out, or discontinue treatment, the reasons for discontinuation and the time of the last dose will be recorded. Completed assessment data will be included in the statistical analyses, whereas incomplete data will be treated as missing. Missing data will be handled using multiple imputation methods.

Predefined subgroup analyses for the primary efficacy endpoint will be conducted by gender, age, TD severity and clinical subtype. Sensitivity analyses will include the impacts of prohibited concomitant medications and poor study drug adherence.

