### Sample size

2.7

To date, no active-controlled trial has evaluated PABG for the treatment of tic disorders with SDPWS. The primary endpoint of this study is the change from baseline in the YGTSS–Tic Severity Score (YGTSS-TTS) at Week 8. Preliminary data from our pilot study indicated a mean baseline YGTSS-TTS score of 22.8. The minimal clinically important difference (MCID) for the YGTSS-TTS is defined as a ≥ 25% reduction from baseline (39), corresponding to 5.7 points. Based on effect sizes reported in clinical trials of comparable Chinese patent medicines for tic disorders (40), and considering the dose-gradient design of the present study, we assume a mean reduction of 8.2 ± 7.0 points in the active control group, 12.4 ± 6.8 points in the low-dose group, and 12.9 ± 6.6 points in the high-dose group.

With a two-sided significance level of *α* = 0.025 (Bonferroni correction for two comparisons: high-dose vs. active control and low-dose vs. active control) and *β* = 0.20 (80% power), and an allocation ratio of 2:2:1, the sample size was calculated using PASS version 20.0 (NCSS, LLC, Kaysville, UT, USA). Allowing for a 15% dropout rate, the adjusted and rounded total sample size was determined to be 150 participants, with 60 in the high-dose group, 60 in the low-dose group, and 30 in the active control group. The primary comparisons are each active dose versus the active control; the sample size was not powered to detect a statistically significant difference between the two active doses. The close projected outcomes (0.5-point difference) reflect a conservative assumption, and the dose–response assessment is exploratory.

The assumed effect size between each active dose and the active control (approximately 4.2 to 4.7 points) is consistent with the effect observed in a previous trial of a similar Chinese patent medicine (40), where the active product showed a 4.8 point greater reduction in YGTSS-TTS compared with placebo at week 8. Although this effect is slightly below the MCID of 5.7 points, as an exploratory dose-finding trial, any statistically significant signal, even if below the MCID, would support further investigation in a larger confirmatory trial. The MCID will be used for clinical interpretation of the final results.

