### Primary efficacy endpoints

3.1

The change in YGTSS-TTS from baseline and the proportion of participants achieving a ≥ 30% reduction in YGTSS-TTS, both assessed at Week 8.

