### Primary outcomes

4.1

The change from baseline in YGTSS-TTS at Week 8 will be compared between groups using analysis of covariance (ANCOVA), with treatment group, baseline value, and randomization stratification factors included as covariates. Least-squares means, standard errors, and 95% CIs for the change scores, as well as least-squares mean differences with 95% CIs between groups, will be estimated.The proportion of participants achieving a ≥ 30% reduction in YGTSS-TTS from baseline at Week 8 will be calculated with 95% CIs using the Wilson score method. Between-group differences in response rates will be estimated with 95% CIs using the stratified Newcombe method, and group comparisons will be performed using the stratified Cochran–Mantel–Haenszel (CMH) test.

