### Limitation

5.1

Although this study will optimize certain shortcomings of the retrieved studies, it will still have limitations.

First, we excluded children with common comorbidities (ADHD, OCD, etc.) to avoid confounding. Psychiatric comorbidities are well-recognized as highly prevalent in tic disorders. Therefore, our findings apply primarily to the subgroup without these comorbidities; generalization to comorbid populations may overestimate the treatment effect and requires separate studies. The present trial is a necessary first step to establish a clean efficacy signal, and future studies will include children with stable comorbidities.

Second, the 8-week treatment and 4-week follow-up are relatively short. Tic disorders, especially transient tic disorder, can show natural improvement over time. However, the randomized controlled design ensures that any such natural improvement would occur equally across all groups. Therefore, a statistically significant difference between either active dose group and the control group would still indicate a genuine treatment effect beyond natural fluctuation. The current design does not allow for meaningful conclusions about the durability of treatment responses. Longer-term follow-up is needed and will be pursued once funding is available.

Third, our eligibility was restricted to children with SDPWS, which accounts for nearly half of pediatric tic disorder cases. If the trial is positive, the findings directly support the efficacy of PABG in this largest TCM subgroup, allowing generalization to nearly half of children with TD. For children with other TCM patterns, the results cannot be directly extrapolated; however, clinicians may consider individualized use based on pattern differentiation, recognizing that efficacy in those groups has not been established by this trial and requires separate investigation.

Fourth, the active control contained 5% of the active herbal ingredients to maintain blinding. Thus, the design tests PABG against a low-dose active control rather than an inert placebo, which may bias efficacy estimates toward the null. Future studies with a fully inert placebo are warranted.

Fifth, the sample size is insufficient to definitively establish a dose–response gradient, but the trial will provide descriptive information on dose-related trends.

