Sixth, all participants were recruited from a single institution that also developed PABG, which may introduce selection and allegiance biases (though blinding and independent monitoring reduce detection bias). As a dose-finding study, a single-center design is acceptable; however, future confirmatory trials should be multicenter and independent of the product developer.

Seventh, a study suggests that fetal sex hormone exposure may play a role in the development of tic disorders (11). This biological subtyping, analogous to TCM syndrome differentiation, could be considered in future research to screen for optimal treatment candidates.

Despite these limitations, this trial will provide high-level evidence from an active-controlled dose-gradient study of PABG in children with TD, enabling an exploratory assessment of the dose–response relationship. If positive, the results could support registration of this in-house preparation under China’s regulatory pathway.

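### The sample-size section fixes one primary endpoint at two-sided 0.025 per dose, but the analysis sections use two primary endpoints at 0.05 with 95% intervals and give no success rule

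*Protocol article*

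**What the plan says.** **Section 2.7 (Sample size).** There is one primary endpoint: "The primary endpoint of this study is the change from baseline" in YGTSS-TTS at Week 8. The two-sided level is 0.025, explained as a "Bonferroni correction for two comparisons: high-dose vs. active control and low-dose vs. active control". The total is 150 (60 high dose, 60 low dose, 30 control), for 80% power and 15% dropout.

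**Section 3.1 (Primary efficacy endpoints).** There are two: "The change in YGTSS-TTS from baseline and the proportion of participants achieving a" 30% or greater reduction, both at Week 8. The abstract agrees with this, and Section 4.2 refers back to a second primary outcome. The subgroup sentence in Section 4 goes back to the singular.

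**Section 4 (Statistical analysis).** One general threshold applies: a two-sided P "value <0.05 will be considered statistically significant, and 95% confidence intervals (CIs) will be used to estimate effect sizes".

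**Section 4.1 (Primary outcomes).** ANCOVA is used for change, "as well as least-squares mean differences with 95% CIs between groups, will be estimated". The responder rate gets a stratified CMH test, also with 95% intervals.

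**Section 5.1 (Limitation).** "If positive, the results could support registration of this in-house preparation" under the national regulatory pathway.

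**The concern.** The document answers two questions in two ways each.

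- **Which level decides a primary contrast?** A P value of 0.04 for one dose on change is negative under Section 2.7 and positive under Section 4.
- **How many primary endpoints are there?** Section 2.7 has one and Section 3.1 has two. With two doses, Section 3.1 gives four primary tests, and the Bonferroni correction covers only the two doses.

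The document also does not say whether one endpoint is enough or both must succeed. Both the false-positive risk and the power depend on that rule. If it is left open until the data are unblinded, whoever writes the report can choose among several definitions of a positive trial, and the sponsor foresees a positive result contributing to registration.

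**Working it through.** **1. The stated level.** 0.05 / 2 = 0.025, which is exact for two dose comparisons on one endpoint. For two doses and two endpoints the same correction would be 0.05 / 4 = 0.0125.

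**2. Inputs from Section 2.7.** Mean reductions are 8.2 (SD 7.0) for control, 12.4 (6.8) for low dose and 12.9 (6.6) for high dose. Mean baseline is 22.8. After 15% dropout, 30 × 0.85 = 25.5 and 60 × 0.85 = 51, so 25/51/51 evaluable were simulated. Assumptions not in the document: change is normal and independent of baseline, and baseline SD is 0 to 5.

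**3. Simple bounds at 0.05.** If all tests were independent, two tests give 1 − 0.95² = 9.75% and four give 1 − 0.95⁴ = 18.5%. The shared control correlates the two dose contrasts at 60/(60 + 30) = 2/3. The two endpoints correlate at about 0.78–0.79 in simulation, because the responder status is cut from the same score.

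**4. Family-wise error when no arm differs** (all arms mean 8.2, SD 7.0):

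| What counts as success | Level per test | Family-wise error |
|---|---|---|
| Change only, either dose | 0.05 | about 8.5% |
| Any one of four tests | 0.05 | about 13% |
| Both endpoints for the same dose | 0.05 | about 4% |
| Change only, either dose | 0.025 | about 4.4% |
| Any one of four tests | 0.025 | about 7% |
| Any one of four tests | 0.0125 | about 3.7% |

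With the shared control kept, the 13% runs from 16.3% (uncorrelated endpoints) to 11.8% (correlation 0.9).

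**5. Responder rates implied by the same inputs.** At the mean baseline the cut-off is 0.30 × 22.8 = 6.84 points.

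- Control: Φ((8.2 − 6.84)/7.0) = 58%
- Low dose: Φ((12.4 − 6.84)/6.8) = 79%
- High dose: Φ((12.9 − 6.84)/6.6) = 82%

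**6. Approximate power, low / high dose** (change by unadjusted t test):

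| Rule for a dose | At 0.05 | At 0.025 |
|---|---|---|
| Change alone | 69% / 80% | 59% / 71% |
| Change and responder rate | 46–47% / 58–60% | 34–36% / 45–48% |

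**7. How much of the shortfall is due to the responder test.** Only part. Change alone at 0.025 is already below 80%. The number of controls needed is n = (SD₀² + SD₁²/2)(z₀.₉₈₇₅ + z₀.₈)²/δ².

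- Low dose: (49 + 23.12) × 9.505 / 17.64 = 38.9, so 39 controls, 195 evaluable, and 195/0.85 = 230 in total.
- High dose: (49 + 21.78) × 9.505 / 22.09 = 30.5, so 31 controls, 155 evaluable, and 155/0.85 = 183 in total.

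Both exceed 150. That is a separate question about the sample size.

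**The case against.** **The trial is exploratory.** Section 2.7 calls it an exploratory dose-finding trial and says a significant signal would lead to a larger confirmatory trial. Section 2.1 calls the dose–response assessment exploratory. This softens the consequence of a false positive. It does not remove the contradiction: the same section chose Bonferroni, and Section 5.1 links a positive result to registration.

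**The SAP may settle it.** A plan not shown can fill a gap. It cannot agree with both 0.025 and 0.05, or with both one and two primary endpoints.

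**0.05 is only a default.** That would be plausible if Section 4.1 set 97.5% intervals for the primary contrasts. It sets 95%.

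**A stronger reading is tempting and should be resisted.** A reader might infer that any one of four tests at 0.05 makes the trial positive, so that the error simply is 13%. Section 5.1 seems to support this where it says that "a statistically significant difference between either active dose group and the control group would still indicate a genuine treatment effect". But that sentence argues that randomization balances natural improvement of tics; it is not a decision rule. The remark in Section 2.7 about any significant signal concerns going on to a further trial and does not say which endpoint. The document has no success rule, and if a dose must succeed on both endpoints the error at 0.05 is below 5%.

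A reader might also blame the responder endpoint for all the lost power. Section 2.7 never claims to have powered that endpoint, and change alone also falls short.

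**Conclusion.** The point holds as an internal contradiction on the significance level and on the number of primary endpoints, made worse by the missing success rule. This rests on the printed text and needs no assumption.

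The size depends on the rule. At 0.05 the family-wise error is about 4%, 8.5% or 13%, so inflation above 5% follows under two of the three readings, not all. The reading that keeps the error below 5% pays in power: under 50% for the low dose and at most about 60% for the high dose, against a stated 80%.

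These figures assume normal change scores independent of baseline, an assumed baseline SD of 0 to 5, and 25/51/51 evaluable. ANCOVA adjustment may recover some power on change, but the document states no correlation from which to compute it.

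**What to change.** Before unblinding, make Sections 3.1, 4 and 4.1 and the abstract agree with Section 2.7:

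- Name change in YGTSS-TTS at Week 8 as the single primary endpoint.
- Test each dose against control at two-sided 0.025 (Bonferroni) and report 97.5% intervals for these two contrasts, so that test and interval agree.
- Make the 30% responder rate a key secondary endpoint, tested for a dose at the same 0.025 level only after that dose has succeeded on change.
- Limit the general 0.05 threshold and 95% intervals to the remaining analyses and label those P values nominal.

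If the sponsor prefers to keep both endpoints as alternative primaries, state that rule and test all four contrasts at 0.0125, which gives about 3.7% family-wise error.

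**Cost.** The change is one of wording, and recruitment is expected to run to 31 December 2026. Compared with testing at 0.05, power on change falls from about 69% to 59% (low dose) and from 80% to 71% (high dose), before any gain from ANCOVA. The responder rate loses primary status. The stricter level is not a new demand, because Section 2.7 already states it.

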### Primary outcomes

4.1

The change from baseline in YGTSS-TTS at Week 8 will be compared between groups using analysis of covariance (ANCOVA), with treatment group, baseline value, and randomization stratification factors included as covariates. Least-squares means, standard errors, and 95% CIs for the change scores, as well as least-squares mean differences with 95% CIs between groups, will be estimated.The proportion of participants achieving a ≥ 30% reduction in YGTSS-TTS from baseline at Week 8 will be calculated with 95% CIs using the Wilson score method. Between-group differences in response rates will be estimated with 95% CIs using the stratified Newcombe method, and group comparisons will be performed using the stratified Cochran–Mantel–Haenszel (CMH) test.

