### Participants information

2.8

Information collected during the screening period will include demographic data (date of birth, gender, ethnicity); TD-related information, including the date of initial diagnosis, date of first medical consultation for TD-related symptoms, frequency and type of past symptoms, disease subtype (TTD, CTD, TS), and a history of prior pharmacological and non-pharmacological treatments for TD; as well as medical history unrelated to TD, a history of pharmacological and non-pharmacological treatments within the 3 months prior to screening, and allergy history.

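### Tic subtype is recorded at screening but left out of the primary ANCOVA, and Section 5.1 claims more for randomisation than it delivers; the cost is precision, not bias

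*Protocol article*

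**What the plan says.** The inclusion criteria (Section 2.4) admit TTD, chronic tic disorder (CTD) and Tourette syndrome (TS) together. The exclusion criteria (Section 2.5) remove only TTD that has lasted 90 days or less. Section 2.8 lists "disease subtype (TTD, CTD, TS" among the screening data, so subtype is known before allocation.

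Section 2.10 stratifies on three age bands and two bands of YGTSS total score. Section 4.1 analyses the Week 8 change in YGTSS-TTS by ANCOVA "with treatment group, baseline value, and randomization stratification factors included as covariates". Subtype is therefore neither a stratum nor a model term. It appears only in Section 4, as one of four predefined subgroup factors for the primary endpoint.

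Section 5.1 accepts that tics, and TTD above all, may remit without treatment. It answers that "the randomized controlled design ensures that any such natural improvement would occur equally across all groups", and infers that a significant difference would show a real effect.

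**The concern.** The protocol names a patient feature that it expects to affect the outcome, collects that feature before randomisation, and then leaves it out of the model for the main estimate. In its place stands a statement about randomisation that is true of the average over repeated trials but not of any one trial. The smallest arm has 30 children, so the realised share of TTD can easily differ between that arm and a dose arm.

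Two things are at stake. One is the accuracy of a sentence on which the authors rest their defence against natural improvement. The other is precision that could be had at almost no cost, in a trial whose control arm is small. Because Section 4.1 spells out the covariates, this is a choice the protocol has made and not a detail left to the statistical analysis plan.

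**Working it through.** **The plan's own figure.** Section 2.7 uses two-sided alpha "0.025 (Bonferroni correction for two comparisons: high-dose vs. active control and low-dose vs. active control", "80% power), and an allocation ratio of 2:2:1", and mean reductions of "8.2 ± 7.0 points in the active control group", "12.4 ± 6.8 points in the low-dose group" and "12.9 ± 6.6 points in the high-dose group". With 2:1 allocation, controls needed = (z_alpha + z_beta)² × (SD_c² + SD_t²/2) / difference².
- Low dose: 9.505 × (49 + 23.12) / 4.2² = 38.9, so 39 controls, 195 in total, and 230 after 15% dropout.
- High dose: 9.505 × (49 + 21.78) / 4.7² = 30.5, so 31 controls, 155 in total, and 183 after dropout.

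The stated 150 is not reproduced. That is a separate matter. It bears here only in showing that precision is not in surplus.

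**Inputs for this point.** Arms of 60 and 30, and a difference of 4.2 points for the low dose, come from Section 2.7. SD 6.9 is the midpoint of 7.0 and 6.8. Two inputs are assumptions that the documents do not supply: the TTD share q, taken as 20-50%, and the extra 8-week improvement d in TTD against the other subtypes, taken as 2-6 points.

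**1. Chance imbalance.** The SD of the between-arm difference in TTD share is sqrt(q(1−q)(1/60 + 1/30)).
- q = 0.2: sqrt(0.16 × 0.05) = 0.089.
- q = 0.5: sqrt(0.25 × 0.05) = 0.112.

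By the hypergeometric distribution for 30 against 60, a gap of at least 10 percentage points has probability 0.40 (q = 0.2) to 0.50 (q = 0.5). A gap of at least 20 points has probability 0.05 to 0.12. With only 10% TTD, the probability of a 10-point gap is 0.26.

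**2. What the imbalance contributes to the estimate.** The 95% range of shift is ±1.96 × SD of imbalance × d.
- Low end: 1.96 × 0.089 × 2 = 0.35 points.
- High end: 1.96 × 0.112 × 6 = 1.31 points.

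**3. Where that shift sits.** The standard error without subtype is 6.9 × sqrt(1/60 + 1/30) = 1.54, so the 95% half-width is 1.96 × 1.543 = 3.02 points. The shift is one component of this half-width. Taking it out in quadrature:
- Low end: sqrt(3.024² − 0.351²) = 3.00, a cut of 0.7%.
- High end: sqrt(3.024² − 1.315²) = 2.72, a cut of 10%.

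**4. The same result as variance explained.** Share = q(1−q)d²/SD².
- Low end: 0.16 × 4 / 47.61 = 1.3%. The standard error is multiplied by sqrt(1 − 0.013) = 0.993.
- High end: 0.25 × 36 / 47.61 = 18.9%. The standard error is multiplied by sqrt(1 − 0.189) = 0.90.

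Steps 3 and 4 agree because they describe one quantity.

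**5. Effect on power, low dose, normal approximation, before dropout.** Power = Φ(4.2/SE − 2.241). Without subtype it is Φ(4.2/1.543 − 2.241) = 0.68. With subtype it is 0.69 at the low end (SE 1.533) and 0.78 at the high end (SE 1.389).

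**6. Validity.** In 20,000 simulated trials per setting with no treatment effect (30 against 60; 30-50% TTD improving 3-5 points more; t test without subtype), the rejection rate was 0.024 to 0.026 against a nominal 0.025. The mean estimated difference was close to zero.

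**7. Subtype as a stratum.** Six strata would become 18, and controls per stratum would fall from 30/6 = 5 to 30/18 = 1.7.

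**The case against.** The planned ANCOVA is standard and valid. Chance imbalance in an unmodelled factor is ordinary sampling error, and the standard error already carries it. This stands in full. A reader might infer that uneven natural improvement biases the comparison or undermines a significant result. The documents do not support that: with type I error at its nominal level, the inference in Section 5.1 from a significant difference survives.

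A reader might also count the possible shift of 0.35-1.31 points and the loss of precision as two harms. They are one. The shift lies inside the 3.02-point half-width and should not be set against the planned 4.2 points as if it came on top.

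The size rests on assumed inputs. Its top end needs half the children to have TTD and a subtype gap of 6 points, which is larger than the planned treatment effect of 4.2-4.7 points. SD 6.9 is also the raw change-score SD, so whatever baseline score and strata already explain reduces the gain. Excluding TTD of 90 days or less may narrow the difference between subtypes. All of this is fair, and the low end of the range is small.

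Nor does the protocol say that subtype determines improvement. It singles out TTD and does not rank CTD against TS. One might add that a child with only motor or only vocal tics can score at most 25 on YGTSS-TTS, while a child with both can reach 50. The baseline score in the model captures much of that, and it does not bear on the TTD calculation.

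The subgroup analysis by subtype and the baseline summaries would let an imbalance be seen, but neither adjusts the main estimate. The objection therefore limits the size of the point. It does not rescue the claim of equality or give a reason to omit the factor.

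**Conclusion.** The point holds as a modest improvement in precision and a correction of wording. Section 5.1 is wrong to treat equal natural improvement as guaranteed, because randomisation secures it only in expectation, and with 30 controls a sizeable chance imbalance in subtype is likely. Leaving subtype out of the ANCOVA does not invalidate the primary analysis. Under the assumed 20-50% TTD and 2-6 points of extra improvement, including it would lower the standard error by about 1-10%, before allowing for overlap with baseline score and strata. If subtype is only weakly prognostic in this population, the gain will be negligible. It would be wrong to conclude that subtype should have been a stratification factor: 18 strata with fewer than two controls each would be unworkable.

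**What to change.** Before unblinding, prespecify clinical subtype (TTD, CTD or TS, as recorded at screening) as an additional fixed covariate in the primary ANCOVA of Section 4.1 and in the ANCOVAs for continuous secondary endpoints in Section 4.2. Leave the randomisation strata as they are.

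Reword Section 5.1 to say that natural improvement is expected to be balanced across groups on average, and that the continuous endpoints are adjusted for subtype. Do not extend that statement to the primary responder endpoint. Its stratified CMH test and Newcombe interval would still not account for subtype, so the claim would be untrue there.

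The cost is a change of text and two degrees of freedom, with no new data. Section 5.2 expects recruitment to end on 31 December 2026, so the change can be made while recruitment is open.
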